### Handling of Multiple Postural Measures

Given the multiplicity of postural parameters assessed, there exists an inherent risk of type I error inflation due to multiple comparisons. To mitigate this, several strategies will be implemented. Although all postural measures are considered exploratory, the analysis will prioritize a core set of clinically relevant parameters identified a priori based on the extant literature, including head-neck inclination, shoulder asymmetry, and lumbar arrow. As an alternative to multiple univariate comparisons, multivariate analysis of variance for repeated measures may be used to compare the overall postural profile between conditions, provided the underlying assumptions are satisfied. For exploratory analyses involving multiple univariate paired comparisons, conservative corrections such as the Bonferroni adjustment or false discovery rate control using the Benjamini-Hochberg procedure will be applied. Findings will be interpreted judiciously, and effect sizes, including Cohen *d* for paired samples, will be reported alongside *P* values to emphasize the magnitude of observed effects rather than relying solely on statistical significance.

### Handling of Missing Data

Minimal missing data are anticipated owing to the standardized data collection protocol. Nevertheless, any missing values in postural measurements, for instance, due to obscured anatomical landmarks in photographic acquisitions, will be systematically reviewed. Should data be determined to be missing completely at random, complete case analysis will be performed. If the proportion of missing data exceeds 5% for a key variable, multiple imputation techniques will be considered, provided the missing at random assumption is tenable. Missing data in questionnaire responses will be addressed in accordance with the scoring manuals of each respective instrument, including the QuickDASH and Neck Disability Index.

### Association With Pain and Disability (Secondary Aims)

To examine factors associated with the outcomes of pain and performance-limiting pain, logistic regression models will be used. The dependent variables will be the presence of pain during the preceding week and the presence of performance-limiting pain during the preceding week, both operationalized as binary outcomes. Independent variables will include demographic characteristics (eg, age and gender), occupational factors (eg, instrument type [classified as symmetric or asymmetric], years of professional experience, and practice hours), and postural delta values, which represent instrument-induced postural changes as described above.

To investigate factors associated with the severity of disability, as measured by the QuickDASH, Oswestry Disability Index, and Neck Disability Index scores, linear regression models (or quantile regression models, if model assumptions are violated) will be used, incorporating the same set of independent variables.

Variables achieving a *P* value of <.10 in univariate analyses will be entered into multivariable models to identify independent predictors. Results will be reported as odds ratios or regression coefficients with their corresponding 95% CIs. A *P* value of <.05 will be considered indicative of statistical significance in all final models.

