**Objective:**

The primary aim of this study (the Orchestral Posture Ergonomic Assessment [OPErA] project) is to quantify postural deviations in professional orchestral musicians, with and without their instruments, and to investigate their association with pain and pain leading to performance limitation. Secondary aims include exploring demographic, clinical, and occupational factors associated with these outcomes.

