### Objectives

The study aims are to investigate the frequency and types of postural changes, both while musicians are playing their instruments and when they are not, and evaluate whether these postural changes are associated with pain and pain leading to performance limitation. The study will also explore additional associated factors with postural changes and pain based on the demographic, clinical, and musical activity information obtained through the questionnaire.

Finally, it will explore how these postural issues affect the professional lives of musicians.

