All information, both personal and clinical, collected during this study is confidential and will be treated in accordance with the relevant regulations. During the research, the following data will be collected: common personal data (first name, surname, and age), lifestyle data (physical activity), professional activity data (eg, instrument played, hours of study or work, and study mode), and health-related data (presence of pain with functional limitation at present or in the past and diagnosis of scoliosis). With the participants’ consent, the data will be entered in pseudonymized form into a computerized REDCap database. Within the digitized database, each patient will be associated with a numeric code (ID) for identification. The key linking participant identities to their corresponding IDs will be stored by the principal investigator on a protected file outside the digitized database for the duration of the study and deleted at the end of the study. Processing operations will be related to research purposes for the conduct of the study. Data will be processed in such a way as to ensure compliance with the principles and requirements established by the EU Regulation 679/2016 and current legislation. Security measures will be implemented to prevent data loss, unauthorized access, unauthorized processing, or any processing that is not consistent with the research purposes described above. Access to and processing of the data will be permitted to the Fondazione Don Carlo Gnocchi’s managers and appointees or authorized persons as well as other personnel involved in the study. Alphanumeric codes will be used to identify the person participating in the study, and only authorized personnel will be able to trace these codes to the participant’s identity. The data collected will be processed and stored by the Foundation for the time necessary to achieve the purposes of the study, after which they will be kept for 10 years from the conclusion of the study itself in the REDCap system, under the responsibility of [name].

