## Discussion

### Anticipated Findings

This study is designed to provide a comprehensive quantitative analysis of postural deviations in professional orchestral musicians and to explore their association with pain and PPL. By systematically comparing posture during instrumental performance and in a neutral, instrument-free condition, the study aims to identify posture-related associated factors, compensatory strategies, and their potential impact on musicians’ health and professional functioning.

Beyond estimating the prevalence of postural alterations, pain, and PPL, this investigation seeks to clarify how instrument-specific demands and asymmetrical playing positions influence musculoskeletal load. The comparison between neutral sitting posture and instrument-related posture is expected to highlight the extent to which musical performance exacerbates or induces postural deviations, thereby contributing to biomechanical strain. This distinction may help differentiate between baseline postural characteristics and those primarily driven by instrumental practice.

The anticipated findings may reinforce existing evidence that prolonged exposure to forced and asymmetrical postures represents a major contributor to musculoskeletal disorders in musicians. Instruments requiring sustained elevation of the upper limbs, trunk rotation, or unilateral loading—such as bowed string and certain wind instruments—are likely to be associated with greater degrees of postural imbalance, particularly at the cervical, shoulder, and scapular levels. These deviations may correlate with higher rates of upper limb and spinal pain, supporting the hypothesis that compensatory postural behaviors act as a key intermediate mechanism linking instrumental demands to PRMDs.

A central aspect of this study is the investigation of compensatory strategies adopted by musicians to meet technical and artistic performance requirements. While these adaptations may allow musicians to maintain performance quality in the short term, they may also increase cumulative musculoskeletal load over time, predisposing individuals to PRMDs. The identification of such compensatory patterns through objective postural measurements may therefore provide clinically meaningful insights that complement self-reported symptoms and disability assessments.

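### The pain and disability models enter posture only as the with-minus-without delta, although the aim covers posture in each condition

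*Protocol article*

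**What the plan says.** The abstract's Objective is to "quantify postural deviations in professional orchestral musicians, with and without their instruments, and to investigate their association with pain". The Objectives section likewise speaks of "postural changes, both while musicians are playing their instruments and when they are not, and evaluate whether these postural changes are associated with pain". Both conditions are therefore part of the question about pain.

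Under Main Comparison, the delta is the value with the instrument minus the value without it. The section calls the deltas the primary measures of playing posture and gives them a key role in the later regressions.

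Under Association With Pain and Disability (Secondary Aims), the logistic models take demographic characteristics, occupational factors "and postural delta values, which represent instrument-induced postural changes as described above". The linear (or quantile) models for QuickDASH, Oswestry and Neck Disability Index scores take the same set. Variables with P<.10 in univariate analysis go forward. No section gives a model that relates posture in a single condition to pain or disability.

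**The concern.** A difference between two conditions does not measure posture in either of them. A musician who is misaligned to the same degree with and without the instrument has a delta of zero and enters the model like one who is well aligned in both. If lasting misalignment is what goes with pain, a delta-only model may show little or nothing. If posture without the instrument is what matters, the delta coefficient can take the wrong sign. The Discussion expects the findings to inform ergonomic interventions and posture education, so a delta coefficient that is wrongly signed or wrongly null could misdirect that advice.

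**Working it through.** **Inputs.** From the article: n=250, two-sided 0.05, delta = with minus without. Its only sample-size figure is a prevalence precision: 1.96 × √(0.25/250) = 0.062, which agrees with the stated 6% after rounding. That figure has no bearing on the pain models, and the article states no power for them. Assumed, because the article does not give them: 50% pain at mean posture, correlation r between conditions of 0.3-0.7, SD ratio k (with/without) of 1 to 2, and the effect sizes below.

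**Algebra.** Let N be a parameter without the instrument, W the same parameter with it, and D = W − N. Let the condition effects be b_N and b_W.

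1. A shift c in both conditions cancels: (W + c) − (N + c) = W − N.
2. Since b_N·N + b_W·W = (b_N + b_W)·N + b_W·D, a model with D alone forces b_N + b_W = 0, that is, equal and opposite effects.
3. With SD(N)=1 and SD(W)=k, the delta-only slope (exact for a linear model, approximate for a logistic one) is [b_W(k² − rk) + b_N(rk − 1)] / (1 + k² − 2rk).
4. At k=1 this is (b_W − b_N)/2 for any r. A with-instrument effect b appears as b/2, a no-instrument effect b as −b/2, and equal effects as 0.
5. The sign for a pure no-instrument effect is that of rk − 1. At k=1.5 it is negative for r=0.3 (0.45 − 1 = −0.55) and about zero for r=0.7 (1.05 − 1 = 0.05). The reversal therefore depends on k and r.

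**Simulation 1.** Odds ratio 1.5 per SD of whichever component drives pain, 1000 runs per scenario, r = 0.3, 0.5 and 0.7. The delta-only test has 1 df. The test with N and D has 2 df.

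| True driver | k | Delta-only power | N and D power | Fitted OR per SD of delta |
|---|---|---|---|---|
| Mean of N and W | 1 | 4-5% | 79-82% | 1.00 |
| W | 1 | 23-47% | 81-83% | 1.17-1.27 |
| N | 1 | 25-44% | 79-82% | 0.79-0.85 |
| D | 1 | 85-88% | 78-81% | 1.49-1.51 |
| Mean of N and W | 1.5 | 22-35% | 80-81% | 1.17-1.22 |
| W | 1.5 | 64-68% | 81-82% | 1.35-1.37 |
| N | 1.5 | 4-19% | 80-81% | 0.87-1.02 |
| D | 1.5 | 86-87% | 80-82% | 1.50-1.51 |

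**Simulation 2.** Effects in log-odds per SD.

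- 0.3 in each condition: delta-only power is about 5% at k=1 and 15-75% at k=1.5-2, against 92-99% with both terms.
- 0.5 with the instrument only: 30-59% against 93-94% at k=1. At k=1.5 delta-only reaches 79-82% and at k=2 it reaches 91-92%, against 93-95%.

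**Signed parameters.** The Methods do not say whether inclinations and asymmetries are signed. If they are, left and right deviations offset each other in any linear term. With pain driven by |N| + |W|, the delta-only model and the two-term model both had only 4-7% power.

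**The case against.** The delta answers a legitimate question. The Objectives ask about postural changes, and between-condition differences are the natural measure of what the instrument induces. If the change itself drives pain, the 1-df delta test beats the 2-df test (82-89% against 75-81% at 0.4 log-odds per SD). Playing may well widen the spread of posture, and the loss is then smaller. The article's wording does not say that the list of terms is closed, it calls all postural measures exploratory, and it places these models under secondary aims. All of this stands, and it limits the severity. It does not supply the missing term: the open-ended examples extend only the demographic and occupational classes, and the delta is the one postural variable named.

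A reader might infer four stronger things that the documents do not support.

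- *That the models cannot test the aim at all.* They test the part that concerns instrument-induced change, and test it well.
- *That the distinction promised under Anticipated Findings ("This distinction may help differentiate between baseline postural characteristics and those primarily driven by instrumental practice") is lost.* In that section it rests on comparing neutral with playing posture, which the paired analysis delivers.
- *That a real posture effect would generally be reported as no association.* That is so only for an effect common to both conditions with equal SDs. Otherwise the loss is partial, and sometimes small.
- *That scoliosis must be added as a covariate.* It is collected ("diagnosis of scoliosis") and clinical factors are among the secondary aims, but a covariate left off a condensed list is no error. Scoliosis may also be part of fixed posture, so adjusting for it could remove the effect being sought.

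**Conclusion.** The concern holds in limited form. The aim covers posture in each condition, while the listed models contain only the difference between conditions. The cancellation of a shared deviation and the mixing of the two effects follow from the definition of the delta and need no assumption. The size of the loss does rest on assumptions. It runs from near-total (power at about the significance level for a common effect with equal SDs) to slight (a with-instrument effect when the with-instrument SD is twice the other). The sign reversal for a no-instrument effect holds at equal SDs and fades as rk approaches 1. This should be fixed, but it does not threaten the study: the models are secondary and exploratory, and the paired comparison does not depend on them.

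**What to change.** In every pain and disability model, for each core parameter named under Handling of Multiple Postural Measures (head-neck inclination, shoulder asymmetry, lumbar arrow), enter the no-instrument value together with the delta. Keep each pair together in the multivariable model, so that the P<.10 screen cannot drop one member. Report the 2-df posture test as well as the 1-df delta test.

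State how the coefficients read. Beside N, the delta coefficient is the effect of with-instrument posture at fixed N, and the N coefficient is the sum of the two condition effects. Entering N and W instead gives the same fit but different coefficients, so the chosen form must be named. For signed parameters where severity is the question, use absolute deviations in each condition.

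Cost: no new data, since both conditions are already measured, and three more coefficients per model if all three core parameters are entered. The interval for the delta becomes slightly wider. If only the change matters, the 2-df test loses about 6-10 points of power, which is why the 1-df delta test is kept. The Results section says full analysis is under way, so the change should be recorded and dated before the pain and disability models are run, or reported as a later addition if they have been.

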#### Sample Size

A total of 250 participants will be enrolled. Regarding the primary objective of the study, which is to investigate the prevalence and types of postural alterations, it is estimated that—assuming a prevalence of 50%—a sample of 250 participants will allow for an estimation of the prevalence with a significance level of α=5% and a precision (semiwidth of the CI) of 6%, using the binomial model with normal approximation for the calculation of the CI.

Participant recruitment will be conducted following ethics committee approval and registration of the study on ClinicalTrials.gov, with an anticipated recruitment period of 30 months.

Participation in the study will be voluntary and will require written informed consent. All musical instruments will be eligible for inclusion and will be classified as either symmetrical or asymmetrical for analysis purposes.

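### Instrument type is adjusted for the postural changes it is expected to cause, so the final models cannot give its overall association with pain or disability

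*Protocol article*

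**What the plan says.** All references are to the protocol article.

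- **Association With Pain and Disability (Secondary Aims), covariates.** Two logistic models are planned, for pain and for performance-limiting pain in the preceding week, "both operationalized as binary outcomes". The occupational factors offered to these models include "instrument type [classified as symmetric or asymmetric], years of professional experience, and practice hours". Age and gender are candidates too. So is a further group of variables in the same list, the "postural delta values, which represent instrument-induced postural changes as described above". Linear or quantile models for QuickDASH, Oswestry and Neck Disability Index scores use the same set, so five outcomes are affected.
- **Same section, entry rule.** Variables with univariate P<.10 "will be entered into multivariable models to identify independent predictors", and P<.05 counts as significant in the final models.
- **Main Comparison.** A delta is the value with the instrument minus the value without it. The deltas are to be key independent variables in the regressions.
- **Anticipated Findings.** The authors expect results that may support the hypothesis that "compensatory postural behaviors act as a key intermediate mechanism linking instrumental demands to PRMDs".
- **Abstract.** Occupational factors associated with pain are a secondary aim, and instrument-specific associated factors are an expected output.

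The article describes no adjusted model without deltas, no mediation analysis, and no distinction between overall and direct association.

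**The concern.** On the document's own account the order is instrument, then posture, then pain. A model that contains both instrument type and the deltas holds the intermediate step fixed. Its instrument coefficient answers a narrow question: do asymmetric-instrument players differ in pain from symmetric-instrument players who have the same postural change? It does not answer whether players of asymmetric instruments have more pain.

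The study also sets out to report on occupational factors, and for instrument type the second question is the natural one. Under the stated rule the only result that addresses it is the univariate one, which is unadjusted and is used for selection. The adjusted result, which readers will take as the finding, could show little or no association because the posture hypothesis is right.

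**Working it through.** **The plan's own figure.** The only sample-size figure is a confidence-interval half-width of 6% for a 50% prevalence with 250 participants: 1.96 × √(0.5 × 0.5 / 250) = 0.062, which rounds to the stated 6%. The point does not depend on it; only n = 250 is carried forward.

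**Structure.** Let I be instrument type (1 = asymmetric) and M a delta in SD units.

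- M = d·I + error (SD 1)
- logit P(pain) = a + bI·I + bM·M

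With M in the model, the coefficient of I is bI. Without M, the log odds ratio for I is approximately (bI + bM·d) / √(1 + 0.346·bM²). The constant is (16√3 / 15π)² = 0.346, from the usual logistic-normal approximation.

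**Assumed inputs.** The documents give no pain rate, instrument share, delta SD or effect size, so d, bM, bI, the share of asymmetric instruments and the pain prevalence are all assumptions.

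**Illustrative case by formula.** Take bM = ln 1.65 = 0.501, d = 1.5 and bI = 0.

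- Without the delta: 0.501 × 1.5 = 0.751; 0.751 / √(1 + 0.346 × 0.251) = 0.751 / 1.042 = 0.721; odds ratio 2.06.
- With the delta: odds ratio exp(0) = 1.00.

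**Simulation, n = 250.** The first two rows assume 60% asymmetric instruments and 60% pain prevalence. The last two span shares of 50% and 65%, shifts of 0.8 to 1.6 SD, bM = 0.6 and pain at about 50%.

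| Scenario | OR without delta | OR with delta | P<.05 without | P<.05 with |
|---|---|---|---|---|
| d = 1.5, no direct effect | 2.06 | 1.00 | 79% | 5% |
| d = 1.0, direct OR 1.22 | 1.94 | 1.22 | 71% | 11% |
| d = 0.8 to 1.6, no direct effect | 1.57 to 2.46 | 0.98 to 1.01 | 39 to 94% | 4 to 6% |
| d = 0.8 to 1.6, direct log OR 0.4 | 2.24 to 3.56 | 1.47 to 1.53 | 87 to 99.5% | 18 to 31% |

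**Is it mediation or only correlation?** With a delta that shifts by 1.2 SD but has no effect on pain, the odds ratio is 1.99 without it and 2.02 with it. Only precision is lost (79% to 66% significant). The attenuation therefore comes from mediation.

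**How often do both variables enter?** In the fully mediated scenarios of the third row, both pass the P<.10 screen in 53 to 97% of runs.

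**Sensitivity to imperfect deltas.** If the delta has reliability r, about (1 − r) of the mediated effect stays on the instrument coefficient. For the illustrative case, r = 0.7 gives exp(0.751 × 0.3) = 1.25 and r = 0.5 gives exp(0.751 × 0.5) = 1.46. If asymmetric instruments shift posture in opposite directions and risk follows absolute deviation, the signed delta mediates little: simulated odds ratios go from 1.73 to 1.73 with an even split of directions and from 1.73 to 1.57 with an 80/20 split. With a shift of only 0.3 to 0.5 SD, the odds ratio is 1.15 to 1.29 before the delta enters, so little can be lost.

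**The case against.** The strongest reply is that the joint model suits the main association question, whether posture is associated with pain. Instrument type can confound that association, so adjusting the deltas for it is right. **This stands**: the posture coefficients are not at fault, nor is the primary within-subject comparison.

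An independent predictor can also mean no more than an association conditional on the other covariates, and the article never calls the instrument coefficient an overall effect. It acknowledges that the design is not causal and that pain may influence posture. **This stands in part.** The acknowledged limitations do not mention adjustment for an intermediate variable, and no other adjusted instrument estimate is described.

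The univariate instrument result is a planned analysis, and joint entry depends on both variables passing the screen. Both statements are true. However, the univariate result is unadjusted, and joint entry is the more frequent outcome in the mediated scenarios simulated.

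Staged models could be left to a statistical analysis plan that is not shown. That would be a full answer if the article were silent, but it states the covariate set, the entry rule and the purpose of the model.

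A reader might infer that the plan will report asymmetric instruments as unassociated with pain, the reverse of what the data show. The documents do not support this. It would need nearly complete mediation by well-measured deltas that shift in one direction. The device is described as not formally validated, the deltas are signed, and the Discussion calls posture a key mechanism, not the only one. A weak instrument coefficient beside a clear delta coefficient and a positive univariate result would also not be the reverse of the data.

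**Conclusion.** The point holds as a limited one about interpretation and reporting in a secondary analysis. When instrument type and the deltas both pass the screen and the deltas carry part of the effect, the final model gives an attenuated instrument coefficient that should not be read as the overall instrument association. The size depends on inputs that the documents do not give. Under complete mediation by an error-free delta, the odds ratio goes from about 2.1 to 1.0, a misleading null for the overall association. With a direct effect or an imperfectly measured delta it is reduced but not removed, and with small or opposing shifts it changes little. The change is worth making because it supplies an adjusted estimate that the stated rule does not give when both variables enter.

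**What to change.** For each of the five outcomes, pre-specify two models.

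- **Model A:** instrument type with age, gender, years of experience and practice hours, without deltas. Report the instrument association from this model.
- **Model B:** Model A plus the deltas, with instrument type always retained whatever its univariate P value. Report the posture association from this model.

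Add one sentence stating that the instrument coefficient in Model B is the part not passing through the included deltas and is not read as the overall instrument association.

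The cost is one extra model per outcome and that sentence. No new data are needed. The article says the full analysis is under way, so the change should be documented and dated before the regression results are examined.
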